#### **4. Follow-up hand hygiene assessment**

Serial follow-up WASH survey will be administered every week and at discharge (from acute COVID-19 daily monitoring) during the daily follow-up phone calls for the HBC study. The follow-up hand hygiene assessment will repeat questions about participant-reported in-home hand hygiene practices. The follow-up questionnaire may also assess the safe usage of the ABHS in the home by asking if there have been any adverse events (e.g. splash in eye or ingestion). This questionnaire is estimated to take 5 minutes. Additionally, to understand behavioral and preferential aspects of different hand hygiene technologies, upon discharge from the period of acute monitoring, 10 patients from each ABHS arm will be selected to complete Hand-Hygiene In-depth Interviews which are estimated to take 5-10 minutes. All patients enrolled in the study are eligible for selection for interviews. The 10 patients will be selected as a convenience sample based on availability of study staff.

#### **5. Exit interview from acute COVID-19 monitoring**

All study participants will be administered an exit interview to understand their opinions and level of satisfaction with the care provided in each study arm. This questionnaire is estimated to take 5 minutes.

#### **6. Acceptability assessment**

Questionnaires will be administered to study staff, triage center staff, and other key stakeholders to assess acceptability of HBC strategies. These questionnaires will explore the acceptability of the two HBC methods in providing care to patients with COVID-19 who are discharged home. A short version of the questionnaire will be used with each category of key respondent, with data stored on a secure database. Then, a longer version of the questionnaire will be administered by study staff during in-depth interviews to further explore any acceptability-related questions and suggestions and to validate initial findings. Better understanding the acceptability of the intervention and how it could be improved will allow better tailoring for larger-scale implementation. The short version of the questionnaire is estimated to take ten minutes, the in-depth interviews are estimated to take 45 minutes.

#### **7. Qualitative WASH assessment**

Questionnaires will be administered to a small group of patients who did and not receive additional ABHS in their COVID Care Kits to assess change in knowledge, attitudes, and behavior related to hand hygiene among patients and their family members during the course of their COVID-19 infection. The questionnaire will take up to 25 minutes and will be conducted over the phone by trained study personnel. All data will be securely stored.

#### **8. Chronic COVID-19 symptoms**

Following discharge from acute COVID-19 daily monitoring, study staff will offer all study participants the opportunity to participate in ongoing COVID-19 symptom monitoring. Study staff may administer phone surveys to study participants every 3 months for up to one year to assess COVID-19 sequelae and use of health services. Participants may be offered a medical assessment during the follow-up period of symptoms monitoring. Data will be collected using a standardized Post-COVID Conditions Questionnaire. Longitudinal follow-up phone surveys to assess for chronic COVID-19 symptoms are estimated to take 5 minutes.

## Indicators

Specific indicators will be used to assess the feasibility, impact and acceptance of the HBC intervention. Primary outcome indicators are designated with “\*”. Although final indicators may be updated and/or modified, the preliminary set of indicators are listed below.

- Feasibility
  - o Proportion that receive the prescribed HBC intervention
  - o Proportion with complete pulse oximetry data, for relevant arm
  - o Proportion lost to follow-up
- Referral to higher level of care
  - o Proportion referred to higher level care due to hypoxia (i.e. SpO2 < 92%)
  - o Proportion referred to higher level care due to alarm symptoms
  - o Proportion referred to higher level care for any other reason
  - o Proportion referred that reach higher level of care within 24 hours
  - o Proportion who successfully complete HBC without requiring referral
  - o Disposition after referral (home, admission, other) \*
  - o SpO2 level upon arrival to higher level of care
  - o Other clinical measures upon arrival to higher level of care
- Impact on patient outcomes:
  - o Duration of hospitalization (days)\*
  - o Duration of ICU and/or ventilator requirement\*
  - o Mortality\*
- Acceptability
  - o Perception of utility/benefit of strategy (study staff/patients)
  - o Perception of ease of implementation of strategy (study staff)
  - o Changes in hand hygiene behavior

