## Sample size for primary outcome indicators

To calculate the power to detect a difference between two specific groups, we used a two-sided test of independent proportions with the statistical parameters of alpha 0.05, beta 0.2, and power of 0.8. The intervention effect was selected to provide clinically and operationally meaningful outcomes. In addition, the power calculations are based on the following assumptions.

- Likelihood of referral for higher care: According to a study on the use of pulse oximeters to determine referral of COVID-19 patients to a higher level of care, 24.7% of patients required such a referral, in a second study 33% of patients using a pulse oximeter at home and receiving remote COVID-19 management were referred. Given that those studies were conducted prior to the availability of vaccines, and 34% of the Honduran population is vaccinated, we will use a baseline estimate that 20% of patients will be referred for higher care, with a greater proportion referred in the group using pulse oximeters, given additional opportunities to detect the need for referral. The ability to detect a 6% absolute difference between referral rates between arms requires an enrollment of 804 patients per arm for a total enrollment of 1,608 participants.
- Likelihood of hospitalization: The most recent published COVID-19 study in Honduras identified a 25% hospitalization rate in the general population, prior to vaccine availability. We estimate that 10% of all enrolled patients will be hospitalized, taking into account increasing vaccination coverage and the high risk status of the enrolled population. The ability to detect a 5% absolute difference in hospitalization rates between arms requires 946 participants per arm for a total enrollment of 1,892 participants.
- Length of hospitalization: Given an average of 7.7 days hospitalization per admitted patient (SD 10.8), a per arm/strategy sample size of 773 is powered to detect a 20% difference in length of hospitalization between groups for a total enrollment of 1546 participants.
- Pulse oximetry: Given an estimated mean SpO2 of 93% (SD 7%) at the time of evaluation at a higher level of care, a per arm/strategy sample size of 85 is powered to detect an absolute difference between groups of SpO2 of 3%, for a total of 255 patients referred to a higher level of care, for a total enrollment of 850 participants.

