## Data analysis

The primary analysis will provide unadjusted and adjusted differences between arms/strategies based on the covariates listed. We will perform additional subgroups analyses, specifically examining age, sex, comorbidities, baseline clinical features, and timing of the interventions. Qualitative analyses will be conducted by trained researchers using Excel to organize data, given the limited sample sizes. Research analysis will adhere to the Sex and Gender Equity in Research (SAGER) guidelines including reporting representativeness, presenting disaggregated results regardless of positive or negative outcome, withdrawal/attrition rates, and implications of reported gender on study results.

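### Four outcomes are starred as primary and alpha 0.05 is undivided, with no deciding outcome, order, split or all-must-succeed rule: false-positive risk up to about 18.5% if any one result counts

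*Protocol*

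**What the plan says.** The Indicators section of the Protocol states: "Primary outcome indicators are designated with" a star. Four indicators carry it. Disposition after referral is listed under referral. Length of hospital stay, "Duration of ICU and/or ventilator requirement" and mortality are listed under "Impact on patient outcomes". The same section calls the list preliminary and open to change.

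The section on sample size for primary outcome indicators opens with one set of error rates for everything that follows: "we used a two-sided test of independent proportions with the statistical parameters of alpha 0.05, beta 0.2, and power of 0.8". It then sizes five outcomes separately: referral, hospitalization, length of stay, SpO2 at the higher level of care, and mortality.

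The Data analysis section says: "The primary analysis will provide unadjusted and adjusted differences between arms/strategies based on the covariates listed". It gives no deciding outcome, no testing order, no division of alpha and no rule that all four must succeed. It also does not say whether the unadjusted or the adjusted estimate leads.

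**The concern.** With four equal primaries, each read against two-sided 0.05, a significant difference on any one of them can be presented as a primary effect of home oximetry. The error rate for that claim is then higher than the 5% used in the sizing. Two co-equal versions of the primary analysis leave a further choice open.

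Objective 3 asks about the utility and impact of oximetry on outcomes, and the results are meant for health authorities. If the four primaries disagree, the protocol does not say which one answers that question. This also cannot be settled later at no cost. The stated sample sizes spend the whole 0.05 on each outcome, so a later division of alpha would leave the stated 80% power unmet.

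**Working it through.** **Inputs from the Protocol**
- Four starred outcomes (Indicators).
- Two-sided alpha 0.05 and power 0.80, so z = 1.960 and 0.842 (sample-size section).
- Stay: mean 7.7 days, SD 10.8, 20% difference, 773 per arm.
- Mortality: 7.5%, difference 3.3 points, 854 per arm.

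The correlation between the four test statistics is not given. It is varied from 0 to 0.9.

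**Step 1. Was the full alpha used?**

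Stay: the difference is 0.20 × 7.7 = 1.54 days. n = 2(1.960 + 0.842)² × (10.8/1.54)² = 772.05, rounded up to 773. Stated: 773.

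Mortality, read as 7.5% v 4.2% (mean 5.85%):
- Uncorrected: m = [1.960√(2 × 0.0585 × 0.9415) + 0.842√(0.075 × 0.925 + 0.042 × 0.958)]² / 0.033² = 792.8.
- Continuity corrected: n = (m/4)[1 + √(1 + 4/(m × 0.033))]² = 852.3, rounded up to 853. Stated: 854.
- The direction is not stated. 7.5% v 10.8% gives 1,198 (1,257 corrected), so 7.5% v 4.2% is the reading that fits.

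With alpha split four ways (0.0125, z = 2.498) and power still 0.80, stay needs 1,097 per arm and mortality 1,187 (corrected). The stated sizes therefore rest on the undivided 0.05.

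**Step 2. How sized and starred outcomes line up**

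| Outcome | Starred | Sized | Reproduced at 0.05 and 80% power |
|---|---|---|---|
| Disposition after referral | yes | only indirectly, through hospitalization (946) | no: 10% v 15% gives 686, or 726 corrected |
| Length of stay | yes | 773 | yes |
| ICU/ventilator time | yes | no | not applicable |
| Mortality | yes | 854 | yes, within 1 |
| Referral | no | 804 | yes: 20% v 26%, corrected, gives 804.05 |
| SpO2 on arrival | no | 85 | yes: 85.5 |

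A four-way split does not explain the 946 either: at 0.0125 the figures are 975, or 1,014 corrected.

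**Step 3. Family-wise false-positive rate, four tests at two-sided 0.05**

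Independent tests: 1 − 0.95⁴ = 0.1855. The upper limit without any assumption on dependence is 4 × 0.05 = 0.20.

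Equal pairwise correlation r: the rate is 1 − ∫φ(u)[Φ((1.96 − √r·u)/√(1−r)) − Φ((−1.96 − √r·u)/√(1−r))]⁴ du.

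| r | 0 | 0.3 | 0.5 | 0.7 | 0.9 |
|---|---|---|---|---|---|
| Rate | 18.5% | 17.4% | 15.6% | 13.0% | 9.4% |

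**Step 4. Power if alpha is divided later**

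Mortality, 854 per arm, on the continuity-corrected basis that reproduces the plan's figure. Solving the correction formula backwards, 854 corresponds to m = 794.5.
- Alpha 0.05: (0.033√794.5 − 1.960 × 0.3319)/0.3311 = 0.845, so power is 0.80.
- Alpha 0.0125: (0.033√794.5 − 2.498 × 0.3319)/0.3311 = 0.306, so power is 0.62.

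Stay, 773 per arm at face value: power falls from 0.80 to 0.62.

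**The case against.** The strongest reply is that this is partly an omission. Multiplicity rules are commonly left to a statistical analysis plan, which is not at hand here. The indicator list is called preliminary, the Data analysis section promises differences rather than tests, and 0.05 appears only as a sizing parameter. The protocol never claims a 5% error rate for its overall conclusion. All of this is true, and it lowers the severity. It does not remove the point. The choice of primary outcomes has been made in the protocol, the sample sizes are built on an undivided alpha, and a plan that later splits alpha contradicts the stated power.

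Four stronger readings are tempting and are not supported:
- **One fixed inflated rate, such as 16%.** That needs a correlation near 0.5. The protocol gives none, and the outcomes have different denominators (referred, admitted, all enrolled), so only a range can be given.
- **A higher rate still, because there are two analyses per outcome.** That requires a rule that either version may be used to claim success. The Data analysis section leaves the lead version open but states no such rule.
- **The primaries are bound to conflict.** The sample-size section expects only more referrals with oximeters: "with a greater proportion referred in the group using pulse oximeters, given additional opportunities to detect the need for referral". Its stay figure is a mean per admitted patient, and more admissions need not lengthen that mean. Conflict is possible, not predicted.
- **Mortality is the obvious single primary.** The Indicators section gives it no time point. Daily monitoring ends about ten days after symptom onset if the patient is free of fever, or at hospitalization. Chart review covers patients who were referred, and later calls are optional. The choice is the sponsor's.

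**Conclusion.** The concern holds in a limited form. The protocol fixes four primary outcomes and an undivided two-sided 0.05, and states no rule for combining them. The undivided alpha is confirmed by calculation for length of stay and mortality. It is not confirmed for the hospitalization sizing, which does not reproduce from its own inputs (a separate matter), and ICU/ventilator time has no sizing to check.

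The family-wise rate is up to about 18.5% for independent tests, about 16% at correlation 0.5 and about 9% at 0.9, which is roughly two to four times 0.05. These figures rest on two assumptions: that any one nominal p<0.05 would be reported as a primary effect, and that the correlation is equal across pairs. A reader should not infer that the trial states and then breaks a 5% overall error rate; it states no overall rate. Because the list is called preliminary and the remedy is mainly wording, this should be fixed but does not by itself invalidate the design.

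**What to change.** Before outcome data are seen, amend the Indicators, sample-size and Data analysis sections as follows.

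1. Name one deciding primary outcome and give it a time point.
2. Name one primary analysis, unadjusted or adjusted, tested at two-sided 0.05. Report the other version as a sensitivity analysis.
3. Make the other three starred outcomes secondary. Either test them in a fixed sequence, each only if the one before is significant, or report them as estimates with 95% confidence intervals and no confirmatory claim.

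This needs no extra participants or data. The cost is that the outcomes made secondary lose stand-alone confirmatory status.

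Alternatively, keep all four as primary, test them by Holm at overall 0.05, and restate the power. The first Holm step is at 0.05/4 = 0.0125. At that level mortality power with 854 per arm is about 0.62 instead of 0.80, and stay needs about 1,097 per arm for 80% instead of 773. These are the least favourable figures, since later Holm steps use a larger alpha. ICU/ventilator time and disposition would also need sizings of their own.

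### The outcomes starred as primary and the outcomes sized as primary do not match, and none of the five enrolment totals is adopted

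*Protocol*

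**What the plan says.** The Indicators section states that "Primary outcome indicators are designated with" a star. Four entries carry one: "Disposition after referral (home, admission, other"), "Duration of hospitalization (days"), "Duration of ICU and/or ventilator requirement" and mortality. The same paragraph describes the whole list as provisional: "Although final indicators may be updated and/or modified, the preliminary set of indicators are listed below".

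The section headed *Sample size for primary outcome indicators* sizes five outcomes, each with its own total:

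- Referral to higher care, 20% baseline and a 6-point difference: "requires an enrollment of 804 patients per arm for a total enrollment of 1,608 participants".
- Hospitalization, 10% of all enrolled and a 5-point difference: 946 per arm, 1,892 in total.
- Length of hospitalization, 7.7 days per admitted patient (SD 10.8) and a 20% difference: 773 per arm, "for a total enrollment of 1546 participants".
- SpO2 at higher-level care, SD 7% and a 3-point difference: 85 per arm, "for a total of 255 patients referred to a higher level of care, for a total enrollment of 850 participants".
- Mortality, 7.5% and a 3.3-point difference: 854 per arm, 1,708 in total.

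No sentence in the protocol adopts any of these totals as the enrolment target.

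**The concern.** Both sections use the label of primary outcome indicators but attach it to different sets. A reader cannot tell from the protocol which results answer the trial's question or how many participants will answer it. A report could lead with referral, which is sized as primary, or with disposition after referral, which is starred as primary, and cite the protocol either way.

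The stated 80% power is attached outcome by outcome, each at its own total. Without one adopted total, no primary has a definite power, and ICU/ventilator duration has none stated at all. The sentence allowing the indicators to change does not exempt the primaries and sets no time limit. That matters more because assignment is evident to participants and callers, since only one strategy uses a home oximeter. (The protocol does not discuss blinding; this is read from the design.)

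**Working it through.** **Step 1. The two lists side by side.**

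| Outcome | Starred (Indicators) | Sized (Sample size section) | Total |
|---|---|---|---|
| Duration of hospitalization | yes | yes | 1,546 |
| Mortality | yes | yes | 1,708 |
| ICU/ventilator duration | yes | no | none |
| Disposition after referral (three categories, among the referred) | yes | no; nearest is the next row | none |
| Hospitalization among all enrolled | no | yes | 1,892 |
| Referral | no | yes | 1,608 |
| SpO2 at higher-level care | no | yes | 850 |

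**Step 2. Reproduce the protocol's figures.** Two-sided alpha 0.05, power 0.8. For proportions, with p̄ the average rate and d the difference:

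- uncorrected n0 = [1.96√(2p̄(1−p̄)) + 0.8416√(p1(1−p1)+p2(1−p2))]² / d²
- continuity-corrected n = (n0/4)[1 + √(1 + 4/(n0·d))]²

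For means, n = 2(1.96 + 0.8416)²·SD²/d².

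- Referral, 20% v 26%: n0 = 771, corrected 804. Stated 804; reproduced.
- Mortality, 7.5% v 4.2%: n0 = 793, corrected 852 to 853. Stated 854; reproduced. The protocol does not print 4.2% or a direction; it is inferred from this match. 7.5% v 10.8% would need about 1,257 per arm, and 9.15% v 5.85% (7.5% as the average of both arms) about 1,059.
- Length of stay: d = 0.20 × 7.7 = 1.54 days; n = 2 × 7.849 × 10.8²/1.54² = 772.05, so 773. Reproduced.
- SpO2: n = 2 × 7.849 × 7²/3² = 85.5. Stated 85; reproduced to rounding.
- Hospitalization, 10% v 15%: n0 = 686, corrected 725. 10% v 5%: n0 = 434, corrected 474. Stated 946; **not reproduced**. 20% v 15% gives n0 = 905, corrected 945, so 946 fits a baseline near 20% and not the stated 10%.

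**Step 3. Mortality power at each total.** For n per arm, the corrected effective size is m = (n·d − 1)²/(n·d²), and power = Φ{[d√m − 1.96√(2p̄(1−p̄))] / √(p1(1−p1)+p2(1−p2))}. With 7.5% v 4.2%, d = 0.033, the middle term is 0.6505 and the denominator 0.3311.

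- n = 425: m = 366.6, d√m = 0.6318, (0.6318 − 0.6505)/0.3311 = −0.056, power 47.7%.
- n = 946: m = 886.4, d√m = 0.9825, (0.9825 − 0.6505)/0.3311 = 1.003, power 84.2%.

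**Step 4. Length-of-stay power at each total.** The mean and SD are per admitted patient, so the number analysed per arm is k = 0.10 × n at the protocol's 10% hospitalized. Power = Φ[1.54/(10.8√(2/k)) − 1.96]. At k = 94.6: 1.54/1.570 = 0.981, giving Φ(−0.979) = 16.4%.

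| Total | Per arm | Mortality power | Admitted per arm at 10% | Length-of-stay power |
|---|---|---|---|---|
| 850 | 425 | 47.7% | 42.5 | 9.6% |
| 1,546 | 773 | 75.7% | 77.3 | 14.2% |
| 1,608 | 804 | 77.5% | 80.4 | 14.6% |
| 1,708 | 854 | 80.1% | 85.4 | 15.2% |
| 1,892 | 946 | 84.2% | 94.6 | 16.4% |

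Reaching 773 admitted per arm at 10% would need 2 × 773/0.10 = 15,460 enrolled. Even at 25% hospitalized, the protocol's general-population figure, 1,892 enrolled gives about 34% power.

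**Step 5. Disposition is a different quantity from hospitalization.** Take 946 per arm, 20% v 26% referred, and assume every admission comes through referral. That leaves 0.20 × 946 = 189 and 0.26 × 946 = 246 referred.

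- If 10% v 15% of all enrolled are hospitalized, admission among the referred is 10/20 = 50.0% v 15/26 = 57.7%. Power for that contrast is about 36% (uncorrected), against about 91% (uncorrected) for hospitalization among all enrolled.
- If 10% are hospitalized in both arms, admission among the referred is 50.0% v 10/26 = 38.5%, with about 67% power to declare a difference although hospitalization is unchanged.
- If 20% are referred in both arms and 10% v 15% hospitalized, power exceeds 99%.

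The hospitalization sizing therefore says nothing definite about the starred outcome. For ICU/ventilator duration no power can be computed, because the protocol gives no mean, SD or difference.

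**The case against.** The best defence has four parts.

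- **The lists overlap.** Two of the four starred outcomes are sized, and admission is one category of the disposition outcome. This stands. A reader might infer that the two sets have nothing in common, and that would be too strong: the defect is a mismatch.
- **The largest figure, 1,892, naturally covers the rest.** That is a common reading, but the protocol does not state it. The figure does not follow from its own 10% and 5 points, and even 1,892 leaves ICU/ventilator duration without stated power and length of stay far short of 80%.
- **The list is preliminary and a SAP may settle it.** A SAP may give final definitions, and it is not at hand. But the protocol has already fixed two conflicting sets under one label, so a SAP would have to overrule one of them.
- **Five requirements are not five planned stops.** This stands. A reader might infer that enrolment could end at any of the five totals, with a by-arm test at each and an inflated type I error. The documents do not support that. The protocol describes no interim efficacy look or stopping rule, and its monitoring dashboard tracks enrolment, follow-up, questionnaire completeness, symptom monitoring and attrition, not outcomes by arm.

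**Conclusion.** The point holds as a contradiction within the protocol. Of four starred primaries, two are sized as such, one is matched only by a related outcome on a different denominator, and one has no sizing. Of five outcomes sized as primary, referral and SpO2 at higher-level care are not starred, and hospitalization among all enrolled corresponds only loosely to a starred outcome. No total is adopted, and the choice moves mortality power from about 48% to about 84%, below 80% at three of the five totals. Length of stay is at about 10% to 16% at every total.

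The mortality figures rest on 7.5% v 4.2% with continuity correction, the second rate being inferred from 854 per arm. By the same formula at 1,892, 7.5% v 10.8% would give about 67% and 9.15% v 5.85% about 75%. The length-of-stay figures assume 10% hospitalized in each arm. The finding concerns an undetermined primary set and sample size; it does not show that the sponsor plans repeated testing or early stopping. It should be resolved before analysis because it decides what the trial can claim.

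**What to change.** 1. Make the two lists identical. Keep as primary only outcomes that are both defined and sized, preferably on all randomised participants: for example hospitalization among all randomised, mortality, or both. Label the rest secondary in both sections. Which outcomes to keep is the sponsor's choice; if ICU/ventilator duration or disposition after referral stays primary, it needs its own sizing on its own denominator.
2. Correct the hospitalization sizing before relying on it. Either restate the inputs that give 946 per arm (about 20% v 15%), or keep the 10% baseline and restate the number (about 725 per arm for 10% v 15%, about 474 for 10% v 5%), naming the direction.
3. State both mortality rates explicitly.
4. Adopt one total enrolment and report the power of each remaining primary at that total, even where it is less favourable.
5. Limit the sentence on updating indicators to secondary ones, or to changes made before any by-arm outcome data are seen.

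The cost is a protocol amendment in wording and no new data collection. Some outcomes lose primary status and some power statements will look worse. Whether enrolment changes depends on the total adopted and the corrected inputs, so it cannot be promised that no extra participants are needed.

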- Mortality: Given an estimated mean mortality of 7.5% among the enrolled population, a per arm sample size of 854, and a total sample of 1708, is powered to detect a difference in mortality rate of 3.3% between groups. The mean mortality rate among people with COVID in Honduras is 2.8% among the general population. Given that the enrolled population will be older and more likely to live with comorbidities for negative COVID outcomes, a higher estimated mortality rate has been used.

| Covariate                                                 | General population (SD) |
|-----------------------------------------------------------|-------------------------|
| Proportion of COVID-19 patients requiring hospitalization | 25%                     |
| Duration of hospitalization                  | 7.7 days (10.8)         |
| SpO2 at time of evaluation at higher level of care        | 93% (7%)                |

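### Three of the four starred primary outcomes exist only in referred or admitted patients, and the oximeter is expected to change who is referred; only mortality compares the arms as assigned

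*Protocol*

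**What the plan says.** The Indicators section of the protocol states "Primary outcome indicators are designated with" an asterisk, and four items carry one:

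- "Disposition after referral (home, admission, other"), under referral to higher level of care;
- "Duration of hospitalization (days"), under impact on patient outcomes;
- "Duration of ICU and/or ventilator requirement", under the same heading;
- mortality.

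The section calls the list preliminary and open to modification.

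The section on sample size for primary outcome indicators uses several denominators. For referral it takes a 20% baseline, "with a greater proportion referred in the group using pulse oximeters, given additional opportunities to detect the need for referral", and sizes for a 6-point difference. For hospitalization it says "We estimate that 10% of all enrolled patients will be hospitalized", a share of everyone enrolled. Length of stay is given per admitted patient (7.7 days, SD 10.8). Mortality is again over everyone: "Given an estimated mean mortality of 7.5% among the enrolled population", and the sample "is powered to detect a difference in mortality rate of 3.3% between groups".

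Under Home-based care strategies, only Strategy 2 patients receive an oximeter at home. Under Referral to higher level of care, saturation below 92% is one of the triggers for referral. The Data analysis section names no analysis set for the starred outcomes.

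**The concern.** A randomised comparison is protected when everyone assigned is counted. It loses that protection when the denominator is a group formed after assignment by something the intervention influences. Disposition is defined among the referred, and one arm has a home referral trigger that the other lacks. The durations are defined among the admitted, who may also differ between arms. If oximeters send additional patients to a triage center and fewer of those additional patients need admission, the oximeter arm shows fewer admissions per referral even though the same number of people are admitted. A primary outcome could then show an apparent benefit, or harm, that nobody experienced.

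The sizing adds a second difficulty. Hospitalization is sized over all enrolled, but the nearest starred item is disposition among the referred, so the outcome that is sized and the outcome that is starred have different denominators.

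**Working it through.** **1. The plan's own figures.** With two-sided alpha 0.05 and power 0.80, (1.960 + 0.842)² = 7.849.

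- Length of stay: 20% of 7.7 is 1.54 days. n = 2 × 7.849 × 10.8² / 1.54² = 772.05, rounded up to 773 per arm, as stated. The mean and SD are per admitted patient, which supports reading this outcome as conditional on admission.
- Referral: 20% against 26% gives 772 per arm without and 805 with continuity correction (stated 804). 20% against 14% gives 647 with correction. The sizing therefore uses an increase in referral, in line with the stated direction.
- Mortality: 7.5% against 4.2% gives 853 with correction (stated 854), over all enrolled.
- Hospitalization: 10% against 15% gives 686, or 726 with correction; 10% against 5% gives 435, or 474. Neither is the stated 946. 15% against 20% with correction gives 945.

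**2. Admission among the referred when admission does not differ.** From the protocol: 20% referred in the control arm, 10% of enrolled admitted, 946 per arm. Assumed: 10% admitted in both arms, every admission passing through referral, and 22%, 24% or 26% referred with oximeters. The protocol expects more referrals but states no expected size; 26% corresponds to its detectable difference.

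Admission per referral = 0.10 / proportion referred, so the control value is 0.10 / 0.20 = 50%, in 946 × 0.20 = 189 patients.

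| Referred with oximeter | Number referred | Admission per referral | Expected z | Chance of p < 0.05 |
|---|---|---|---|---|
| 22% | 208 | 45.5% | 0.91 | 15% |
| 24% | 227 | 41.7% | 1.70 | 40% |
| 26% | 246 | 38.5% | 2.41 | 67% |

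For the last row, the pooled proportion is (94.6 + 94.6) / (189.2 + 246.0) = 0.435. SE = √[0.435 × 0.565 × (1/189.2 + 1/246.0)] = 0.0479, and z = 0.1154 / 0.0479 = 2.41. With 804 per arm (161 and 209 referred) the chance is 60%.

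If the extra referrals were admitted at the same 50%, both arms would show 50% and the gap would be zero.

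**3. Length of stay among the admitted.** Assume the oximeter adds 2 admissions per 100 enrolled, each of 3 days. The mean stay becomes (10 × 7.7 + 2 × 3) / 12 = 6.92 days, down from 7.7. Hospital days per enrolled patient rise from 0.77 to (77 + 6) / 100 = 0.83. With 946 per arm, 94.6 and 113.5 are admitted, so SE = 10.8 × √(1/94.6 + 1/113.5) = 1.50 and z = 0.78 / 1.50 = 0.52. Rejection rises only from 5% to about 8%. Range of the shift in the mean:

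- 5 extra admissions per 100 at 3 days: −20%;
- 5 extra at 5 days: −12%;
- 5 extra at 7.7 days: no shift.

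**4. Stay over everyone.** Count zero days for patients not admitted, with 10% admitted. The mean is 0.77 and the variance is 0.10 × (10.8² + 7.7²) − 0.77² = 17.0, so the SD is 4.12. A 20% difference (0.154 days) then needs about 11,253 per arm, and 773 per arm gives about 11% power.

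**The case against.** The best defence is that the denominators are inferred. The Indicators section lists names in a set it calls preliminary, and the sizing of hospitalization over all enrolled may show that admission over everyone was intended. A statistical analysis plan not at hand could say so, or could count zero days for patients not admitted. This has some force for disposition. It has less for length of stay, which the protocol itself sizes per admitted patient. The text as it stands still stars an item whose name restricts it to the referred.

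Three stronger readings are tempting, and the document does not support them.

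- A reader might infer that the trial has no randomised primary comparison. Mortality is starred and sized over the enrolled population, so it remains a comparison of the arms as assigned.
- A reader might infer that the protocol predicts 26% referral and hence a 67% false-positive rate. It predicts a greater proportion only. Six points is what it is sized to detect, and 67% is the top of the range shown.
- A reader might infer that the extra referrals must be mild, so that the bias favours the oximeter by design. The added trigger is low saturation, and the Background says both that marked hypoxia may precede severe illness and that oximetry can identify patients who can safely stay at home. The direction of the severity shift is not fixed. For admissions, the protocol gives only a 5-point detectable difference without a direction.

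**Conclusion.** The point stands for the three conditional outcomes. It is firmest for disposition after referral, because the protocol itself expects the oximeter to enlarge the referred group. Under the stated assumptions (10% admitted in both arms, all through referral), the difference in denominators alone produces a gap in admission per referral of 4.5 to 11.5 percentage points and a rejection rate of about 15% to 67% at 946 per arm. It produces none if the extra referrals are admitted at the control rate.

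For the durations the weakness is one of principle, and its size is uncertain. Direction and amount depend on the severity of any extra admissions, which the protocol does not give, and the modest example adds only about 3 percentage points to the nominal 5%.

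**What to change.** In the Indicators section:

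1. Replace the starred disposition item with hospital admission (yes/no) among all randomised patients. This matches the denominator already used to size hospitalization.
2. Keep mortality starred, and state that it is over all randomised patients.
3. Make disposition after referral, and the durations among the admitted, descriptive. Alternatively, report hospital and ICU days over all randomised patients as secondary outcomes, with zero for those not admitted and an explicit rule for deaths.
4. Restate the 946 per arm from the admission rates actually assumed. It exceeds the 686 (726 corrected) needed for 10% against 15%, but its basis should be visible.

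The first change costs little. Charts are already abstracted for hospitalized patients, and the national identification number is already collected to link hospital visits in the health ministry's (SESAL) database.

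There are two limits. All-randomised duration has low power (about 11% in the working), so it should not lead. A fixed window such as 28 days is more than a change of wording: daily monitoring ends about ten days after symptom onset once fever has cleared, or at hospitalization, and later calls are optional and three-monthly. Such a window should be adopted only if record linkage or existing contacts give vital status to that day.
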